### Classification of CMD disease outcomes

The CMD disease outcomes, hypertension, obesity, diabetes, kidney disease and dyslipidemia, were categorized as below.

#### Hypertension

Classification of hypertension was guided by the JNC7 guidelines of the Joint National Committee of Prevention, Detection, Evaluation, and Treatment of High Blood Pressure [59]. As such, hypertension was defined as the presentation of one or more of the following conditions: previous diagnosis by a healthcare provider (which excluded cases of hypertension during pregnancy), taking medication for the condition, systolic blood pressure greater than 140 mm Hg and/or diastolic blood pressure greater than 90 mm Hg at the time of the study visit [60].

#### Obesity

Body Mass Index (BMI, kg/m^2^) was calculated as both a continuous variable, and categorized according to the standards adopted by the WHO [61], using the following cutoffs: underweight (BMI < 18.5 kg/m^2^), normal weight (BMI ≥ 18.5 and < 25kg/m^2^), overweight (BMI ≥ 25 and < 29.9 kg/m^2^) and obese (BMI ≥ 30 kg/m^2^).

Waist-to-hip ratios were derived by dividing the waist circumference (mm) by the hip circumference (mm), and the results interpreted in accordance with the standards adopted by the WHO [62]. Substantially increased risk of metabolic complications were judged as high if the waist-to-hip ratio (WHR) was ≥ 0.9 for men, and ≥ 0.85 for women.

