#### Physical (anthropometric) measurements

Standing height to the nearest millimetre was measured using a Harpenden digital stadiometer (Holtain, Wales) fixed to a wall. Participants were either barefoot or wearing thin socks. Where possible heels, buttocks, shoulders and the back of the head were touching either the wall or the vertical board of the stadiometer. If this was not possible, a straight posture was maintained with at least the buttocks and heels touching the vertical board. Heels were positioned together with the medial borders of the feet forming a maximum angle of 60°, shoulders relaxed but straightened, and arms hanging freely alongside the body with palms facing inwards. The head was positioned in the Frankfurt Horizontal Plane and the participant asked to take a deep breath and maintain an erect posture. The headboard was brought down onto the vertex of the head with sufficient pressure applied to compress the hair, and care taken not to push the subject down.

Weight was measured to the nearest 0.1 kg using digital Physician Large Dial 200 kg capacity scales (Kendon Medical, South Africa). Participants were asked to remove shoes, heavy clothing and jewellery, and to empty their pockets prior to mounting the centre of the platform, with a 10 cm gap between their heels, leaving arms hanging loosely at their sides.

Waist circumference was measured using a stretch-resistant tape measure (SECA, Hamburg, Germany). Participants were asked to wear only light clothing, with outer clothing removed to enable the tape to be positioned correctly; with the participant standing up straight with arms slightly abducted, and breathing normally, the tape was placed horizontally around the narrowest part of the torso, about halfway between the iliac crest and the lowest rib. Measurement of waist circumference was taken at the end of a normal expiration. Waist circumference was recorded in millimetre. The same tape was used to measure hip circumference, with the tape placed around the most protruding part of the buttocks, ensuring that the zero mark was to the participant’s side. Hip circumference was recorded to the nearest millimetre.

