#### Diabetes

Classification of diabetes was guided by the standards set by the American Diabetes Association [63]. It was defined as the presentation of one or more of the following conditions: previous diagnosis by a healthcare provider (which excluded gestational diabetes), taking medication for the condition, or a fasting blood glucose level of ≥ 7.0 mmol/l. Participants were defined as pre-diabetic if the levels of fasting blood glucose were between 5.6 mmol/l and 7.0 mmol/l.

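### The printed BMI classes leave 29.9 to below 30 in no class, and the pre-diabetes rule overlaps the diabetes rule for diagnosed or treated participants

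*Protocol article*

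**What the plan says.** **BMI.** Under Obesity, the protocol article states that BMI "was calculated as both a continuous variable, and categorized according to the standards adopted by the WHO [61". The lower classes are "underweight (BMI < 18.5 kg/m^2^), normal weight (BMI ≥ 18.5 and < 25kg/m^2" and the upper ones "overweight (BMI ≥ 25 and < 29.9 kg/m^2^) and obese (BMI ≥ 30 kg/m^2". No rounding before categorizing is mentioned. The inputs are fine-grained, according to the section on physical measurements: "Standing height to the nearest millimetre was measured" and "Weight was measured to the nearest 0.1 kg".

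**Glucose.** Under Diabetes, a participant is diabetic on any one of three grounds: a previous diagnosis (gestational diabetes apart), or "taking medication for the condition, or a fasting blood glucose level of ≥ 7.0 mmol/l". The next sentence reads: "Participants were defined as pre-diabetic if the levels of fasting blood glucose were between 5.6 mmol/l and 7.0 mmol/l". It does not say whether the end points are included, or whether participants who are already diabetic by diagnosis or medication are set aside first.

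**The concern.** A set of classes should place every participant in exactly one of them. The BMI scheme fails this because one interval has no class. The diabetes and pre-diabetes pair fails it because some participants satisfy both definitions.

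If the printed rules are run literally, the BMI percentages do not add to 100% and overweight is slightly understated. Pre-diabetes would also count people with known diabetes whose fasting glucose happens to lie in the range. That error runs in one direction: it can only raise the pre-diabetes count. The article is the methods reference for a dataset that is shared externally and harmonized with a larger resource. A user who codes from it has to invent a rule for these people.

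**Working it through.** The plan gives no figure to reproduce here. The check applies the stated inequalities at boundary values and then gauges how many people could be affected.

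**1. BMI, at the stated resolution.** Formula: weight (kg) / height (m)². At a height of 1.600 m, height² = 2.56.
- 76.5 kg: 76.5 / 2.56 = 29.88, overweight.
- 76.6 kg: 76.6 / 2.56 = 29.92, no class.
- 76.7 kg: 76.7 / 2.56 = 29.96, no class.

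The gap is therefore reachable with ordinary measurements. The joins at 18.5 and 25 leave no gap, because each upper bound is the next lower bound. Only the join at 29.9/30 fails.

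**2. Size of the BMI gap.** The document gives no BMI distribution, so a normal distribution with assumed mean and SD is used: share = Φ((30 − mean)/SD) − Φ((29.9 − mean)/SD), multiplied by the 10,702 participants aged 40–60.

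| Assumed mean (SD) | Share in gap | Of 10,702 |
|---|---|---|
| 21 (3.5) | 0.04% | 5 |
| 23 (5) | 0.30% | 32 |
| 25 (6) | 0.47% | 51 |
| 27 (6.5) | 0.55% | 59 |
| 30 (7) | 0.57% | 61 |
| 33 (8) | 0.46% | 50 |

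**3. Glucose, the two definitions side by side.**

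| Fasting glucose (mmol/l) | Known or treated diabetes? | End points included | End points excluded |
|---|---|---|---|
| 5.6 | no | pre-diabetes | neither |
| 6.5 | no | pre-diabetes | pre-diabetes |
| 6.5 | yes | **both** | **both** |
| 7.0 | no | **both** | diabetes |
| 7.0 | yes | **both** | diabetes |

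The overlap for a diagnosed or treated participant at 6.5 does not depend on how the end points are read. The overlap at exactly 7.0 does.

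**4. Size of the glucose overlap.** The document gives neither the prevalence of known diabetes nor the glucose distribution within it. Both percentages below are assumptions.
- Low: 10,702 × 2.5% × 20% = 53.5, about 54.
- High: 10,702 × 4% × 30% = 128.4, about 128.

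**The case against.** Several objections have weight. The 29.9 bound looks like a drafting slip, since the other BMI joins in the sentence are contiguous. The outcome named in the section is obesity, and BMI of 30 or more is untouched, as are analyses of continuous BMI. For glucose, the sentence before the pre-diabetes rule assigns 7.0 and above to diabetes, so excluding the upper end point is the natural reading. An analyst may also remove diabetics first without saying so. Diabetes, not pre-diabetes, is in the list of named outcomes, and the diabetes manuscript was still in preparation.

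These arguments limit the consequence but do not remove the defect. The document prints the operators itself, so this is not detail left to a fuller plan. The natural reading of 7.0 does nothing for the diagnosed or treated participant at 6.5. The Diabetes section does spell out one exclusion (gestational diabetes), so an unstated order of precedence cannot be taken for granted.

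A reader might infer two stronger points, and the document supports neither.
- *That the hypertension rule has the same fault.* It uses "systolic blood pressure greater than 140 mm Hg and/or diastolic blood pressure greater than 90 mm Hg at the time of the study visit", a strict inequality, where the glucose and obesity rules include the limit. But hypertension is a single yes/no outcome, so every reading falls in exactly one class. Different operators for different outcomes are not a contradiction. The article names a guideline as its guide without stating that guideline's cut-points, so no mismatch can be shown from the text.
- *That centres coded the classes differently.* The data capture and quality control section describes transfer to one central database with locked versions. It mentions no centre-specific outcome code.

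**Conclusion.** Two classification rules are wrong as written, and the point is minor.

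The BMI gap is certain from the text. Its size, 0.04% to 0.57% (about 5 to 61 of 10,702), rests on assumed normal distributions. It slightly understates overweight and leaves the obese class and continuous BMI as they are.

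The overlap of diabetes and pre-diabetes for diagnosed or treated participants holds under either reading of the end points. Its size, about 54 to 128 people, rests on two assumed percentages. A value of exactly 7.0 mmol/l adds to it only if the end points are included. The overlap can only inflate pre-diabetes and leaves diabetes prevalence unchanged.

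The article does not show whether the printed rules were executed literally. The finding therefore concerns the stated rules and does not demonstrate an error in the dataset.

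**What to change.** - **BMI:** define overweight as BMI ≥ 25 and < 30, so that its upper bound meets the document's own lower bound for obesity, as the other joins already do. The four classes then cover every value once and the unclassified share is zero.
- **Pre-diabetes:** state whether each end point is included, in a way that does not overlap the diabetes threshold, and limit the class to participants who meet no diabetes criterion. Double classification is then zero.
- **Dataset:** check how the derived variables were coded. If the printed rules were used, re-derive the BMI and pre-diabetes classes and issue a new locked version.

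The cost is two wording changes, a check of the code and possibly a re-run. The overweight and pre-diabetes prevalences would move slightly.

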#### Diabetes

Classification of diabetes was guided by the standards set by the American Diabetes Association [63]. It was defined as the presentation of one or more of the following conditions: previous diagnosis by a healthcare provider (which excluded gestational diabetes), taking medication for the condition, or a fasting blood glucose level of ≥ 7.0 mmol/l. Participants were defined as pre-diabetic if the levels of fasting blood glucose were between 5.6 mmol/l and 7.0 mmol/l.

#### Kidney disease

As an indication of the presence and stage of kidney disease, we assessed the urine albumin/creatinine ratio (ACR) as mg albumin/mmol creatinine [64]. For men, normal was < 2.5, early stage kidney damage (microalbuminuria) 2.5–25, late stage kidney damage (macroalbuminuria) > 25. For women, normal was < 3.5, early stage kidney damage (microalbinuria) 3.5–35, late stage kidney damage (macroalbuminuria) > 35. Calculated eGFR was used as supporting evidence of kidney disease and will be reported in a separate paper.

#### Dyslipidemia

Dyslipidemia was defined as the presence of one of the following indications: self-reported history of high cholesterol, previous diagnosis of dyslipidemia by a healthcare provider, taking medication for the condition, measured total cholesterol level ≥ 5.0 mmol/l, LDL-C ≥ 3.0 mmol/l, and HDL-C < 1.0 mmol/l for men and < 1.3 mmol/l for women, or triglycerides > 1.7 mmol/l, and non-HDL-C > 3.4 mmol/l [65]. These data will be reported in a separate paper.

### Data and sample storage

The AWI-Gen data and samples will be shared with the global scientific community according to the informed consent provided by the participants, in line with the ethics approvals and according to the H3Africa policies and guidelines (www.h3africa.org). In addition to access through direct collaboration, applications can be made to access the data through the European Genome Phenome Archive (EGA) and the samples through an H3Africa Biobank, by applying to the H3Africa Data and Biospecimen Access Committee.

## Results

### Age and country distributions of the AWI-Gen participants

During the period from 2012 to 2016, a total of 10,702 participants between the ages of 40 to 60 years were enrolled across the six AWI-Gen centres, and a further 1021 over the age of 60 enrolled at the Agincourt centre. Following community engagement and individual informed consent, data and samples were collected according to the procedures described above. Age and gender of participants, stratified by participating research centre, are shown in Figure 2, and stratified according to age groups (40–44, 45–49, 50–55 and 55–60 years) in Figure 3.

**Figure 2. F0002:**
[figure not shown]
Distribution of the AWI-Gen study participants across the six centres located in Nanoro (Burkina Faso), Navrongo (Ghana), Nairobi (Kenya), and Dikgale, Agincourt and Soweto in South Africa (SA). The pie charts represent the total numbers of female (orange segments) and male (blue segments) participants aged 40–60 years for each centre, and participants over the age of 60 years for Agincourt.

**Figure 3. F0003:**
[figure not shown]
Distribution of female (orange bars) and male (blue bars) study participants aged between 40 and 60 years across the six AWI-Gen centres, stratified according to age group 40–44, 45–49, 50–54 and 55–60 years.

### Challenges and how we addressed them

Developing and implementing a complex multi-regional epidemiological and genomic study across SSA presented a series of challenges. These are grouped under the four categories described below.

#### Limited ethical and legal frameworks for genomic biobanking research

To address the absence of legal and ethical frameworks and guidelines for large-scale genomics studies in the African countries where the AWI-Gen study is taking place, we convened a workshop in December 2012 for members of ethics committees from the four countries involved. We specifically addressed four areas of concern: community engagement and information sharing; informed and broad consent; sample and data sharing; and benefit sharing [29]. This workshop was important in highlighting the need for further discussion and education of committee members about genomic and biobanking research. It was important in the facilitation of the ethics review process for the AWI-Gen centres to inform and support ethics applications to each of the institutional or national review committees for the AWI-Gen centres in Burkina Faso, Ghana, Kenya and South Africa. It should be noted, however, that the time taken to approach and receive approval from the committees was substantial, and delayed entry to the field by approximately a year.

We worked in concert with the Human Research Ethics Committee (Medical) and the sub-committee for Biobanking Ethics of the University of the Witwatersrand to develop a framework within which our study could operate. This resulted in the development and approval of the SBIMB Biobank that operates according to international norms and standards and is described in a publication providing guidelines on establishing a biobank in a resource-poor environment [21].

Members of the AWI-Gen group provided significant input from personal experience toward the development of H3Africa Guidelines for community engagement and informed consent (www.h3africa.org). Our protocols were included in an analysis of H3Africa Consortium consent documents [66] and we contributed to discussions on promoting fairness for genomic research in an African context [30].

#### Data collection and QC

The use of paper-based questionnaire instruments brings a series of operational challenges. Data clerks need to transcribe the information into electronic form, which then needed to be double checked for errors. At the time there were limited options available to the study, as centres lacked the computer infrastructure, internet connectivity and the system administration support required for electronic capture. With recent advances in the development of REDCap, and simplified network administration tools using LINUX operating systems, there is now no real justification to remain with paper-based tools, except for use as a backup in the case of computer failure.

#### Achieving recruitment targets

Overall, the study sites did a remarkable job of recruiting the required participants according to the inclusion criteria (Figures 2 and 3). One of the AWI-Gen centres, Dikgale in South Africa, failed to reach their recruitment target of 2000 participants between the ages of 40 and 60 years, comprised of roughly equal numbers of women and men. This was because many men of working age temporarily move to the urban regions to seek jobs. They then either live far away for extended periods or only return home on weekends and are then reluctant to spend a day participating in a research project. Of the 1165 participants recruited, ~ 70% were female. The challenge was only realized late in the study, and it was not possible to extend the window for recruitment further. The Agincourt site recruited 1465 participants between the ages of 40 and 60 years with ~ 60% females, and recruited an additional 1021 participants over the age of 60 years, with ~ 53% being female.

#### Blood draw

At several centres, a number of participants expressed dismay and discomfort at the number of tubes of blood that were taken. During community engagement meetings with local chiefs, we learnt that it is very important to carefully explain exactly what each tube of blood would be used for, and to work with the local community leaders to help quell any rumours that the procedure was bad for your health.

### Feedback of biomarker test results

Although those with high blood pressure were referred to their local healthcare providers, we did not do any point of care testing. At the end of Phase 1 of the AWI-Gen study, feedback of potentially clinically relevant information was provided to participants, but since the time lapse between the fasting venous blood collection and the laboratory results was several years, the results were not of health benefit. If fasting glucose or lipid levels were of concern, the data feedback was accompanied by a recommendation to follow up with a local healthcare practitioner. BMI was reported and all participants were encouraged to practise a healthy lifestyle in terms of diet and exercise.

## Discussion

### Building a baseline to describe CMD in SSA

Collection of health data across communities and regions in SSA is key to developing an understanding of the diversity and patterns of NCD burden. However, the differing languages and cultures, varying norms and practices of healthy living, hugely disparate levels of poverty, and the heterogeneity between rural and urban communities make direct comparison of findings a challenge. To begin to explore and understand the interacting factors related to CMD risk and its endpoints, we collected demographic, health, wealth and behavioural data and biomarkers in six African communities that span East, West and Southern Africa. The breadth of data we have obtained will allow us to determine associations with disease and modifiable factors such as BMI, fat distribution and physical activity, together with biomarkers of disease and disease endpoints.

The importance of the baseline data generated from this study has been demonstrated in several recent publications, including the identification of regional and sex differences in the prevalence of hypertension across SSA [60], and the six papers on BMI distribution in this special edition of *Global Health Action* [67–72]. Manuscripts discussing the prevalence of diabetes, body composition and obesity, dyslipidemia, kidney disease, and smoking and alcohol consumption are currently in preparation.

The methods described here take into consideration other CMD cohort studies, providing an opportunity for further harmonization with other studies, and for meta-analyses examining specific research questions expanding over multiple studies. At the outset, the variables were harmonized with the HAALSI study [33], but they have now also been transformed for equivalence with the Cardiovascular H3Africa Innovation Resource (CHAIR) which includes approximately 53,000 individuals [73].

### The need for an engaged community

Planning research that is conducted in a respectful manner, and which reaps maximum social value, is one of the fundamental goals of community engagement [29]. In this study, centres reached out to communities to discuss the nature of the research, how confidentiality would be maintained, and how individual rights as a participant would be protected. One major challenge with genomics research is that scientific language can be abstract and difficult to understand [74]. This meant that field staff had to develop verbal constructs to explain, for example, what genes are and how they are inherited, and to be able to distinguish between diseases that are monogenic or are polygenic and multifactorial in nature. An important concern was that the study might introduce therapeutic and diagnostic expectations [75,76]. Participants were informed that if there were clear clinical indications of disease, then they would be referred to a local medical practitioner or health facility for treatment according to local standards of care. As the nature of diseases being studied by AWI-Gen are primarily polygenic and multifactorial in nature, disclosure of genome-wide association studies (GWAS) and/or whole genome sequencing results would not benefit the individual, and therefore it was made clear to participants that they would not receive individual genetic results. This would include incidental findings of known pathogenic variants. Since our participants are older adults, early onset monogenic traits would already have manifested clinically and would not be detected as new conditions in this study. This being said, if monogenic disease-causing variants for which there is effective treatment are found in the future, then the situation would be addressed in close consultation with the H3Africa ethics advisory committee, and the respective ethics review committees for AWI-Gen and the field research centres.

### A requirement for broad consent, data storage and biobanking

In their paper examining broad consent for genomic research and biobanking in low- and middle-income countries [77], Tindana and de Vries reviewed whether it was morally acceptable to ask that participants provide samples for broad use and sharing within the scientific community. They found evidence to support earlier work that indicated that this could be justified provided that researchers were trustworthy, the research was accompanied by community engagement, and that appropriate governance structures were in place [78]. They also identified a concern that revisiting participants for reconsent for each new study was impractical. In the AWI-Gen study, participants were asked to provide broad consent, under the condition that strict regulatory conditions were in place, and any new studies of the participant samples would need to be approved by an ethics review board. The participant has the right to request removal from the study at any time. This would entail the destruction of specimens held in each of the biobanks and no additional data being generated. It would not be possible to remove data from databases once it had been submitted to an international data repository such as the European Genome-phenome Archive (EGA).

